## Abstract

**Background:**

To date, Siewert type II adenocarcinoma of the esophagogastric junction (ST-II AEG) can be removed radically utilizing either the abdominal-transhiatal (TH) or the right thoracoabdominal (RTA) approaches. Because of a paucity of high-quality direct evidence, the appropriate surgical approach for ST-II AEG remains debatable. In the present, only several retrospective studies are available, representing ambiguous results. Thus, prospective randomized clinical trials are demanded to compare the survival, oncological outcomes, safety and efficiency and life quality between the TH and RTA approach in patients with resectable AEG of Siewert type II.

**Methods:**

A prospective, multicenter, open, randomized, and parallel controlled study named S2AEG will be conducted. Three hundred and twelve patients who match the inclusion criteria but not the exclusion criteria will be participating in the trial and randomly divided into the TH (156) and RTA (156) cohorts. The primary efficacy endpoint is the 3-year disease-free survival (DFS) following the operation. The rate of R0-resection, the number and site of lymph nodes infiltrated and dissected, postoperative complications, hospital days and life quality are the second endpoints.

**Discussion:**

This study is the first prospectively randomized controlled trial aiming to compare the surgical outcomes between TH and RTA approaches in patients with resectable ST-II AEG. It is hypothesized that patients in the TH cohort would harvest equivalent oncological results and survival while maintaining acceptable life quality when compared to patients in the RTA cohort. Our findings will provide high-level clinical evidence for clinical decision-making on the appropriate surgical approach for patients with ST-II AEG. Embarked in November 2019, this research will be completed 3 years after the final participant’s enrolment date.

**Trial registration:**

Clinical Trial.gov ID: NCT04910789 May 29, 2021. Name: S2AEG.

## Background

Adenocarcinoma of the esophagogastric junction (AEG) was defined as the tumor whose epicenter was located 5 cm above and below the junction of the esophagogastric junction (EGJ) [1]. In the duration of the past thirty years, the incidence of AEG has a tremendous increase in both Eastern and Western countries [2–6]. Take America for example, there has been an approximately 2.5-fold elevation in the past 35 years [6]. There is a high incidence of gastric cancer in Asian countries, and a single-center large-capacity study carried out by the West China Medical Center also showed that the proportion of AEG in China increased from 22.3% to 35.7% from 1988 to 2012 [7]. Because of the particularities of the anatomical location and biological behavior, Siewert type II AEG (ST-II AEG) with an epicenter located in 1 cm above to 2 cm below the EGJ, is characterized by a higher degree of differentiation, deeper invasion, higher metastasis rate and worse prognosis compared with other sites of gastric cancer [8]. After the operations with further therapy, the patients’ 5-year overall survival rate remains weak and staggers at around 37.9% to 52.3% [9–13]. Curative surgical intervention is still recognized as the cornerstone of multimodal treatment strategies. Therefore, determining the optimal treatment is imperative to improve the patients’ prognoses.

In order to provide the best therapeutic schedule for ST-II AEG patients, a suitable surgical strategy should ensure both complete resection of the original tumor and adequate dissection of the regional lymph node. Regarding the prevalently adopted Siewert classification worldwide, most researchers have reached a consensus that for patients with ST-I AEG and ST-III AEG the optimal surgical approaches are the transthoracic and abdominal-transhiatal (TH) approaches, respectively [1, 14–16]. However, a constantly controversial opinion is illustrated on the optimal surgical approach taken by ST-II AEG [1, 17, 18]. Some experts prefer the TH approach [10, 12], while others favor the thoracoabdominal (TA) approach [19, 20]. Additionally, the surgical methods of the TA approach differ in Eastern and Western countries. Western countries where the standard approach is thoracotomy on the right side (Ivor–Lewis) (RTA), while Asian countries traditionally are apt to the approach of thoracotomy on the left side (LTA). Previous studies have shown that the TA approach can obtain sufficient safety proximal margins and adequate mediastinal lymph node dissection, while harboring the higher postoperative complication rate as well as longer hospital stay [10, 12, 19, 21, 22]. The more vital part is investigating the effects on prognosis. For ST-II AEG, the optimal surgical approach remains unclear considering the oncological outcomes, quality of life (QOL) and survival, as few high-quality randomized controlled trials have been conducted presently [12, 23, 24]. Moreover, most of the available studies are heterogeneous designs and investigate different surgical approaches including not only ST-II but also ST- I or III [12, 23, 24]. No randomized controlled trials (RCTs) on the RTA and TH approaches have been published so far except for an RCT comparing the TH and LTA approaches [10]. It remains a hot point in dispute in present guidelines without clear recommendation [25].

Based on the above, a prospective, multicenter, randomized, and parallel controlled trial named S2AEG is designed to assess the survival, oncology outcomes, and QOL between the TH and RTA surgical approaches for resectable ST-II AEG.

## Methods

### Objective

This clinical trial is oriented toward comparing the safety, feasibility, and clinical efficacy of the TH and RTA surgical approaches for resectable ST-II AEG. The primary endpoint is defined as the 3-year disease-free survival (DFS), and the secondary endpoints include the rate of R0-resection, the number and station of lymph nodes (LNs) dissected and infiltrated, postoperative complications, duration of hospitalization and QOL. It is hypothesized that the TH approach would produce undifferentiated oncological results and survival for patients with ST-II AEG when compared to those with the RTA approach, while still harvesting satisfactory QOL.

### Study design

S2AEG is designed as a prospective, multicenter, randomized, open, and parallel controlled study conducted in China. This trial is funded by the Program for the Bethune Charitable Foundation (2019–12) and has been registered on Clinical-Trial.gov (NCT04910789, named S2AEG). All the Institutional Ethics Review Committees of participating research centers have approved this protocol. Any amendments that may affect the trial will be further communicated to obtain approval among the Institutional Ethics Review Committees. All researchers will conduct this trial in line with the Declaration of Helsinki and Good Clinical Practice guidelines. Before recruitment, each participant will provide written informed consent for the acquisition and use of anonymized clinical data. This study will be conducted by surgeons who are competent in performing both approaches. None of the patients, surgeons, or data analysts will be blinded.

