### Study population

The clinical efficacy of the TH and RTA approaches for the resectable ST-II AGE, which is the aim of the study. The eligibility of all patients will be determined by their surgeon.

The inclusion criteria are described briefly below:Aged 18–75;Histologically confirmed as Siewert type II AEG;Clinical stage ranges cT1-4aN0-3 M0 (According to the 8th AJCC TNM staging system) and is confirmed by the preoperative examinations (Gastroscopy, enhanced or not computer tomography (CT), magnetic resonance imaging (MRI) or positron emission tomography with CT (PET-CT)).The operation will be performed by either TH or RTA approach according to the direction of the research center and the surgeon;American Society of Anesthesiologists (ASA) physical status score of 1–3;Eastern Cooperative Oncology Group (ECOG) performance status of 0–1;Laboratory test criteria: hemoglobin > 90 g/L, white blood cell > 3 × 10^9/L, platelets > 100 × 10^^9^/L, serum albumin (ALB) > 30 g/L, renal function (serum creatinine (Scr) < 1.5 × ULN and glomerular filtration rate > 60 ml/min), and liver function (alanine transaminase (ALT) and aspartate transaminase (AST) less than 2.5× upper limit of normal);Informed consent of patients is required.

The exclusion criteria are as follows:Siewert type I or III AEG;Postoperative pathological types confirmed as non-adenocarcinoma or non-simple adenocarcinoma;Distant metastasis (M1) or invasion of the peritoneum;Clinically significant central nervous system disease that may influence compliance;Clinically significant diseases (Irregularly controlled diabetes and hypertension; History of myocardial infarction or cerebral infarction within 6 months before the operation; Heart function: New York Heart Association (NYHA) class II or higher; Respiratory function: Forced expiratory volume in the first second (FEV1) < 50%; Liver function: Child-Pugh class C; Renal function: Serum creatinine (Scr) > 1.5xULN and glomerular filtration rate < 60 ml/min;History of gastrectomy (including endoscopic mucosal resection or submucosal dissection);Diagnosed with other malignancies within 5 years;Pregnancy or breast-feeding;Tumor-related complications (dysphagia, gastrointestinal bleeding, perforation, obstruction, etc.) requiring emergency surgery;Being assessed by the investigator as unsuitable for the trial;Persistent withdrawal from clinical trials.

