### Management and quality control

The surgeons participating in this study must meet the following conditions. Each surgeon must have performed the TH and RTA methods in at least 20 cases of AEG surgery and must have passed the qualification examination conducted by three experts in gastrointestinal surgery. Surgeons who want to perform minimally invasive or robotic surgery must prove that they have achieved the operation more than 20 times in a fixed surgical team recently. For a smooth and successful clinical trial, the researchers in all participating institutions must be experts in gastrointestinal surgery to avoid learning curve bias, which is the reason for strict institution invitation and quality control procedures. The pathologist who evaluated the specimens is blind to the surgical approaches because the rate of R0-resection and the status of LNs are the main results of this trial. Patients will be informed of the surgery group they are assigned to. If the patients refuse, they will accept the standard treatment plan of the relevant department.

Throughout the trial, ongoing surgical quality assurance will be undertaken. During each operation, photographs of the surgical details, including the lymphadenectomy region and the fresh specimens following the procedure, will be taken. As a result, these pictures will be used for constant feedback to validate the rationale of the surgical approach, the quality and adequacy of the lymphadenectomy and the integrity of the specimens. They will also be utilized by the research committees to examine and monitor the operation’s quality.

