### Statistical analysis

IBM SPSS (Version26, Chicago, USA) will be used for statistical analysis. If the continuous variable is normally distributed, it will be presented as the mean (standard deviation, SD) with t-tests, or as the median (interquartile range, IQR) with Mann-Whitney U tests if it is not. Categorical variables will be provided as frequency (N) with percentage (%) and assessed using the chi-square or Fisher’s exact test. The Kaplan–Meier curves with the log-rank test will be used to compare the groups’ survival. A bilateral *p*-value of 0.05 or less is deemed to be statistically significant.

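### Data analysts are declared unblinded although coding the arms would be cheap; a minor, avoidable risk of bias in an open surgical trial

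*Protocol article*

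**What the plan says.** The Study design section describes an open, randomized, parallel-group trial and then adds: "None of the patients, surgeons, or data analysts will be blinded". It gives no reason for including the analysts.

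Other sections bear on this:

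- **Management and quality control.** One role is masked: "The pathologist who evaluated the specimens is blind to the surgical approaches". The stated reason is that R0 resection and node status are main results.
- **Statistical analysis, continuous variables.** "If the continuous variable is normally distributed, it will be presented as the mean (standard deviation, SD) with t-tests". Variables judged not normal are instead summarized by medians and compared by Mann-Whitney.
- **Statistical analysis, categorical variables.** These are "assessed using the chi-square or Fisher’s exact test".
- **Statistical analysis, survival.** Kaplan-Meier curves with the log-rank test are named outright, with no alternative.
- **Study population.** The exclusion criteria include "Postoperative pathological types confirmed as non-adenocarcinoma or non-simple adenocarcinoma", which can be known only after randomization and operation. The same section gives the eligibility decision to the patient's surgeon.

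**The concern.** An open surgical trial has to accept that patients and surgeons know the arm. It does not have to accept this for the people who run the analysis. The article fixes the point explicitly, so it is a stated choice and not a detail left to an analysis plan that is not shown.

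The choice matters because some decisions fall after the data exist. Someone must judge whether length of stay or a quality-of-life score counts as normally distributed, and whether chi-square or Fisher applies. Someone must also settle how patients excluded on postoperative pathology enter the analysis set. The investigators have declared what they expect: similar oncological results with the transhiatal approach, and acceptable quality of life. Knowing which arm is which while making such calls lets that expectation influence them, even unintentionally. At stake is some credibility of the secondary comparisons and of the analysis set, in a trial that aims to provide high-level evidence.

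**Working it through.** The plan states no figure on this point, so there is none to reproduce. The check has two parts: which decisions are exposed to open labels, and how large the effect of test choice could be.

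**1. Which decisions are exposed**

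| Decision | What the article fixes | Exposed to an unmasked analyst? |
|---|---|---|
| Test for disease-free and overall survival | Log-rank, named in advance | No |
| Test for continuous secondary outcomes (hospital stay, node counts, quality of life) | Depends on observed normality | Yes, to the extent that normality is a judgement |
| Test for categorical secondary outcomes | Chi-square or Fisher | Yes, slightly |
| Exclusion on postoperative pathology | Specimen read by a masked pathologist; eligibility decided by the surgeon | Not assigned to analysts; they could be involved only when the analysis set is drawn up |

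**2. Size of the test-choice risk**

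Inputs from the article: 156 per arm (Sample size calculation) and a two-sided 5% level (Statistical analysis). Assumptions: no true difference, and outcomes that are either normal or log-normal with sigma 0.6. The article gives no distribution for any outcome.

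Three quantities were simulated:

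- fixed test: P(p_t ≤ 0.05) or P(p_MW ≤ 0.05)
- smaller p-value always taken: P(min(p_t, p_MW) ≤ 0.05)
- normality rule followed: use p_MW if normality is rejected, otherwise p_t

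The first two, from 20,000 null trials with 156 per arm (simulation standard error √(0.05 × 0.95 / 20,000) ≈ 0.15 points):

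| Distribution | t-test | Mann-Whitney | Smaller p-value | Excess over t-test |
|---|---|---|---|---|
| Normal | 4.9% | 4.9% | 5.9% | 1.0 point |
| Log-normal, sigma 0.6 | 4.7% | 4.7% | 6.8% | 2.2 points |

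With 140 per arm (156 × 0.9 ≈ 140, after the article's 10% dropout) the log-normal case gives 4.8% for either fixed test and 6.9% for the smaller p-value.

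The third quantity, from 6,000 null trials with 140 per arm (standard error about 0.28 points). Normality is taken as rejected if a Shapiro-Wilk test is significant at 5% in either arm, which is an assumption because the article names no criterion:

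- At sigma 0.6, normality is rejected in essentially every trial, so the rule leads to Mann-Whitney each time. The type I error is about 5.0%.
- For sigma from 0.2 to 0.8, the rule gives 4.6% to 5.4%, which is 5% within simulation error. Always taking the smaller p-value gives roughly 6.5% to 7.5%.

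So the plan as written keeps the nominal level. The excess of about 1 to 2 points appears only when the rule is not followed. Coding the arms changes no sample size, power or nominal alpha. The effect of discretion over the analysis set cannot be calculated from the document.

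**The case against.** The strongest case against is that this is largely a preference. The article openly describes an open-label trial and contradicts nothing. Masking the pathologist for a stated reason does not commit the plan to masking wherever possible. Test rules and analysis sets are ordinary content of an analysis plan, and fixing them in advance would remove much of the same risk. All of this stands, and it keeps the point minor. It does not supply a reason for ruling out masked analysts.

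Some stronger readings are tempting, but the document does not support them:

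- **That the plan inflates the type I error to nearly 7%.** That figure describes always taking the smaller p-value. The Statistical analysis section lets normality choose the test. For clearly skewed data such as length of stay, that rule leaves almost no discretion.
- **That the primary comparison is exposed to test choice.** The log-rank test is named in advance.
- **That analysts decide who is excluded after surgery.** No section says so. The surgeon determines eligibility and the pathologist is masked. An exclusion made after randomization may be a flaw in its own right, but that is a separate question which coded labels would not settle.
- **That all outcomes are already assessed openly.** R0 resection and node status are read by a masked pathologist.
- **That coding would remove the bias at no cost.** The added thoracic incision, mediastinal node stations or pulmonary events may reveal the arm, and someone must hold the key.

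**Conclusion.** The point holds as a minor, cheap improvement. The article states that analysts will be unblinded when they could be masked, and some analysis choices are made after the data are seen. The result is an avoidable risk of bias, with no bias demonstrated.

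Test choice touches secondary outcomes only. For continuous ones the type I error is near 5% if the normality rule is followed, and about 6 to 7% at worst if the plan is not followed. These figures rest on assumed normal or log-normal outcomes and an assumed normality check. Any effect through the analysis set, which could reach the primary comparison, cannot be quantified. An unseen analysis plan that fixes tests and analysis sets would shrink the benefit further, but would not change the Study design sentence.

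**What to change.** Change the sentence in the Study design section so that only patients and surgeons are described as unblinded. Add that analysts receive the arms coded A/B from whoever manages the central database, with surgical details that identify the arm withheld where feasible. The code is broken only after the analysis set, the test for each outcome and the primary result have been fixed.

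The cost is one sentence and a recoding of the arm variable at database lock. Someone other than the analyst must hold the key; this can be existing data-management staff. Sample size, power, treatment and visits are unchanged. The change can still be made at any time before the data are analysed by arm.

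The gain has limits. Masking will be imperfect because node stations or pulmonary events may hint at the arm, and coding does nothing about open assessment of recurrence or quality of life.

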### Study population

The clinical efficacy of the TH and RTA approaches for the resectable ST-II AGE, which is the aim of the study. The eligibility of all patients will be determined by their surgeon.

The inclusion criteria are described briefly below:Aged 18–75;Histologically confirmed as Siewert type II AEG;Clinical stage ranges cT1-4aN0-3 M0 (According to the 8th AJCC TNM staging system) and is confirmed by the preoperative examinations (Gastroscopy, enhanced or not computer tomography (CT), magnetic resonance imaging (MRI) or positron emission tomography with CT (PET-CT)).The operation will be performed by either TH or RTA approach according to the direction of the research center and the surgeon;American Society of Anesthesiologists (ASA) physical status score of 1–3;Eastern Cooperative Oncology Group (ECOG) performance status of 0–1;Laboratory test criteria: hemoglobin > 90 g/L, white blood cell > 3 × 10^9/L, platelets > 100 × 10^^9^/L, serum albumin (ALB) > 30 g/L, renal function (serum creatinine (Scr) < 1.5 × ULN and glomerular filtration rate > 60 ml/min), and liver function (alanine transaminase (ALT) and aspartate transaminase (AST) less than 2.5× upper limit of normal);Informed consent of patients is required.

The exclusion criteria are as follows:Siewert type I or III AEG;Postoperative pathological types confirmed as non-adenocarcinoma or non-simple adenocarcinoma;Distant metastasis (M1) or invasion of the peritoneum;Clinically significant central nervous system disease that may influence compliance;Clinically significant diseases (Irregularly controlled diabetes and hypertension; History of myocardial infarction or cerebral infarction within 6 months before the operation; Heart function: New York Heart Association (NYHA) class II or higher; Respiratory function: Forced expiratory volume in the first second (FEV1) < 50%; Liver function: Child-Pugh class C; Renal function: Serum creatinine (Scr) > 1.5xULN and glomerular filtration rate < 60 ml/min;History of gastrectomy (including endoscopic mucosal resection or submucosal dissection);Diagnosed with other malignancies within 5 years;Pregnancy or breast-feeding;Tumor-related complications (dysphagia, gastrointestinal bleeding, perforation, obstruction, etc.) requiring emergency surgery;Being assessed by the investigator as unsuitable for the trial;Persistent withdrawal from clinical trials.

### Patient screening

The flow chart of this research is presented in Fig. 1. Multidisciplinary evaluation and standard clinical staging will be done for each patient before enrollment. Based on the anatomical location of the tumors revealed by gastroscopy and the results of the pathological examination of biopsy tissues, the tumors will be classified according to Siewert classification. Imaging examinations (CT, enhanced CT, MRI or PET-CT) will be conducted for determining whether the tumor has distal metastasis and invasion. Complete preoperative preparation also includes anamnesis, demographic information, physical examination, vital signs and laboratory tests.

**Fig. 1 Fig1:**
[figure not shown]
Flow chart

### Inclusion and randomization of patients

On the completion of the baseline assessment and clinical staging, the criteria for inclusion and exclusion will be validated. Informed consent of all participants must be obtained in this trial. Subsequently, the participants will be further divided into the TH cohort or the RTA cohort in a ratio of 1:1 according to the computer-generated random numbers. Then these participants will receive the operation within 1 week after randomization.

